#### Outcomes and participant timeline

2.2.3.

First, during the enrolment assessment, a standardized neurological clinical interview for Parkinson’s Disease (Supplementary material 4) will be performed. This interview includes questions related to habits, disease start, education, and working life. At the same time, weight, height, and body mass index will be measured with a wall stadiometer and a TANITA SC-240MA scale. The length of the lower limbs will also be measured during standing position with a tape measure from the anterior superior iliac spine and the medial malleolus. Asymmetries between the lower extremities greater than 1 cm will be considered within the first exclusion criteria (comorbidities that affect balance or gait). As mentioned above, each phase of the study has three evaluation moments: baseline (T0), post-8-week-training (T1), and follow-up (T2) at 8 weeks after the physiotherapy programs have finished. Assessments will be performed by a different physiotherapist from recruitment and treatment besides a neuropsychologist, both blinded to the treatment assignment. The participants will be evaluated in an ON-medication state (1 h after the dopaminergic dose) on the schedule described in Figure 1. In each measurement session, the severity of the disease (Hoehn and Yahr, 1967; Fahn et al., 1987), cognitive and mental status (Hamilton, 1959, 1960; Mahieux et al., 1995; Dubois et al., 2000; Marinus et al., 2003), perception on quality of life (Peto et al., 1995; Powell and Myers, 1995; Sandín et al., 2020), and balance and gait performance will be registered through clinical tests (Tinetti, 1986; Giladi et al., 2000; Kegelmeyer et al., 2007; Franchignoni et al., 2010) as well biomechanics instruments. Table 2 shows the scales and clinical tests that will be used to evaluate the participants. For balance biomechanics, assessment will be used a dynamometric platform (Dinascan/IBV Biomechanics Institute of Valencia, Valencia, Spain) and the NedSVE®/IBV software (version 5.3.0.1, Biomechanics Institute of Valencia, Valencia, Spain). Balance will be assessed through the Romberg tests under four static conditions with increasing difficulty (see Figures 2A,B): (i) eyes open; (ii) eyes closed; (iii) eyes open on a foam rubber; and (iv) eyes closed eyes on the foam rubber (thickness of 9 cm, 56.7 kg/m3 of density, and resistance of 25%) (Escamilla-Martínez et al., 2021). Participants were asked to find the most stable position while barefoot with their arms relaxed on either side of the body, with their heels together and toes apart at a 30° angle. Additionally, four static functional balance tests will be assessed, using the Romberg test protocol with their eyes open: (i) to see the time on an analogy clock (visual); (ii) to answer a simple question (verbal); (iii) to pour the contents of one glass into another (lower motor); and (iv) to simulate comb the hair (upper motor). The instructions for each task were standardized to ensure uniform execution of the gesture. Participants will be asked to remain as still as possible with their heads in a neutral position and their gaze forward, except for the lower motor test where they will be allowed to observe their hands. Each test will last for 30 s and will be recorded two times. Finally, dynamic balance will be assessed with stability limits and rhythmic weight shift tests on the platform (Balaguer García et al., 2012). In the stability limits test, participants from the Romberg position will have to move a cursor (which reflected the position of their CoP) toward eight targets (front, front-right, right, rear-right, rear, rear-left, left, and front left) visualized on a computer monitor placed in front at their eye level. Once the target is reached, the subject will have to maintain the posture with the CoP displaced at the limit of stability until the end of the 8 s of each test (Balaguer García et al., 2012). On the other hand, in the rhythmic weight shifts tests, subjects will have to move their CoP to the direction and velocity of a moving target visualized on the computer monitor (Balaguer García et al., 2012). Each dynamic test will be registered two times. As a result, the primary outcome of the study will be the CoP sway area, which is defined as the surface over which the CoP moves during the measurement and is a valid indicator of detecting postural control changes in dual-task conditions (Campolettano et al., 2020; Morenilla et al., 2020). The secondary outcomes are shown in Table 2 and consist of biomechanics and clinical variables related to static and dynamic balance.

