**Figure 2 fig2:**
[figure not shown]
Static balance test. **(A)** Protocol for the Romberg test without a foam rubber and for the visual, verbal, lower and upper motor static functional test. **(B)** Protocol for the Romberg test with a foam rubber under the feet. **(C)** Gait model composed by tuberosity of fifth metatarsal (5MTT), posterior surface of calcaneus (CAL), greater trochanter of the femur (GT), lateral condyle of the knee (LC), and lateral malleolus of the ankle (LM).

In addition to balance assessment, the gait of participants will also be measured in a 10 m-long, straight and flat walkway by NedAMH+®/IBV software (v1.1.1, Institute of Biomechanics of Valencia, Spain) which uses two red-light photocells to measure gait speed besides a 3D photogrammetry system with 12 smart-cams (Kinescan®/IBV, version 5.3.0.1, Biomechanics Institute of Valencia, Valencia, Spain), and the dynamometric platform mentioned above. The biomechanical gait model aims to measure movement in the sagittal plane and is made up of 10 landmarks (5 on each leg), located at the anatomical points in Figure 2C. A total of 10 walking repetitions will be analyzed, of which five corresponded to the force data of the right footprint and the other five to the left footprint. Participants will be allowed to walk along the corridor a few times before recording their gait (San Martín Valenzuela et al., 2020a,b). The outcomes from the gait biomechanical assessment are shown in Table 2, and they represent the tertiary outcomes of this study along with those outcomes related to the quality of life, cognitive and mental state, and severity of PD.

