#### Sample size and recruitment

2.2.4.

The software G*Power v.3.1 (Faul et al., 2007) has been used to determine the necessary sample size to detect a change in the primary outcome CoP sway area and differences between the groups (EG, PCG, ACG), with a small-medium effect (*f* = 0.15), a statistical significance of 5% at the two-tailed level, and a power of 95%. As a result of the above, 93 people diagnosed with PD will be recruited. If 20% of possible dropouts are also considered during the study, the initial recruitment should be 112 people. The sampling process will consist in the consecutive non-probabilistic method, in which the selection of individuals is carried out based on the fulfillment of participation criteria. The recruitment of participants began on 1 July 2021 and we estimate its completion on 31 July 2023. The participant recruitment procedure consists of three steps. First, the neurorehabilitation center has selected the possible candidates for the study based on personal and clinical characteristics, asks them by email the authorization to send information about the study, and contacted them using their telephone number. Then, the principal investigators called potential candidates to resolve possible doubts and confirm their participation. Finally, a physiotherapist will assess the selection criteria for all the volunteers and will provide informed consent for their signatures. The recruitment process will be repeated to complete the number of participants estimated for the study, extending participation to a new clinical center or public hospital if necessary.

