### Data collection, management, and statistical analysis

2.4.

Both evaluators (physiotherapist and neuropsychologist) will be responsible for exporting and filling in a database with variables from the scales and tests mentioned in Table 2 according to the code assigned to each patient to ensure his or her anonymity. To protect confidentiality during the study, the personal information of participants will be located separately from the main dataset on a local computer. The raw dataset will be maintained for 10 years after the completion of the trial with indefinite restricted access due to sensitive data. After the publication of the results trial, a fully anonymized patient-level dataset will be made publicly available on the registration trial website (clinicaltrials.gov). For participation in this study, no participant will receive any kind of incentives or compensation.

All analyses will be evaluated by intention-to-treat principles in terms of assignment to treatment and used a level of significance of 0.05. There are no interim analyses planned for this study. We will use the statistical software SPSS Statistics version 24.0 (IBM Corporation) for all the statistical analyses. Categorical variables were presented using frequency and percentage, and continuous variables as mean with standard deviation if they follow a normal distribution. To test for possible carryover effects of the experimental group, the sum of the values measured in the two periods for each subject will be calculated and compared across the two randomized groups (EG and PCG) using a test for independent samples (Serrao et al., 2019). There should be no difference if there is no sequence (balanceHOME program—usual daily activity or usual daily activity—balanceHOME program) effect.

To answer to the main aim of the study, a two-factor mixed multivariate analysis of variance (MANOVA) test was conducted to analyze the effects of within-subject factors (assessment times) and the between-subject factor (group) on the outcomes registered. The Bonferroni adjustment was used for *post-hoc* comparisons, and differences were declared statistically significant if the value of *p* was less than 0.05. Differences between groups for demographic outcomes were verified with a univariate analysis of variance (ANOVA) between-subjects test. Furthermore, to test for sex differences between groups, a chi-square analysis was used (San Martín Valenzuela et al., 2020b).

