
Another relevant aspect is that this protocol aims to solve is the inclusion of dual tasks in the evaluation of balance. Biomechanical balance is usually evaluated as single-tasks on the dynamometric platform (Smania et al., 2010; Kara et al., 2012; Santos et al., 2017; Soke et al., 2019). Complementing the static balance test with dual tasks would provide results of balance performance in real-world situations. Previously, the impact of dual tasks on the gait of trained and untrained people with PD has been determined, finding that verbal secondary tasks have a greater impact on motor performance than visual or motor secondary tasks with the arms (San Martín Valenzuela et al., 2020a,b). In this way, the balanceHOME protocol pretends to resolve methodological issues and research questions relevant to the advancement of physical rehabilitation of balance in the population with Parkinson’s disease.

This protocol will make it possible to facilitate highly challenging functional balance exercises for people with PD at their homes, using common materials of daily use. Similarly, the objective assessment methodology and the balanceHOME protocol will allow us to identify small changes in the balance performance of people with different stages of disease severity and to determine the effectiveness of the home program in people without and with cognitive impairment, which has not been done until now as we will be able to establish the scope that physiotherapy has when it is applied in patients with motor and cognitive failures. Unlike the authors who report improvements below 50% in objective parameters, we think that the structured and progressive dynamics of balanceHOME program can exceed these values of improvement in both dynamic and static balance in single and dual conditions, while performing secondary cognitive and motor tasks of the arms during standing balance maintenance. Furthermore, due to the convenience of home rehabilitation, we think that the effects may achieve better retention during the follow-up period than standard control therapy. This protocol aims to promote change in functional balance physiotherapy both in evaluation and rehabilitation, bringing day-to-day conditions closer to clinical practice.

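### One 0.05 rule covers every recorded outcome: the primary, secondary and tertiary tiers play no part in the testing, and no adjustment across about 43 non-primary variables is stated

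*Protocol article*

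**What the plan says.** The protocol article names one primary outcome, CoP sway area, and powers the trial on it with "a statistical significance of 5% at the two-tailed level, and a power of 95"%. Section 2.2.3 then defines two lower tiers. For the second tier: "The secondary outcomes are shown in Table 2 and consist of biomechanics and clinical variables related to static and dynamic balance". For the third, speaking of the gait biomechanics: "they represent the tertiary outcomes of this study along with those outcomes related to the quality of life, cognitive and mental state, and severity of" the disease.

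Section 2.4 gives the analysis. All analyses follow intention to treat and "used a level of significance of 0.05". For the main aim, a two-factor mixed MANOVA (time within subjects, group between subjects) is applied to the recorded outcomes without distinction of tier. The next sentence has two halves. The first applies a Bonferroni adjustment to post-hoc comparisons. The second says that "differences were declared statistically significant if the value of *p* was less than 0.05".

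The section does not say that the MANOVA must be significant before single outcomes are read, how many MANOVAs there are, or that any tier is exploratory.

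**The concern.** The tiers are labels only. A tertiary gait angle is declared significant by exactly the rule that applies to sway area. The ordinary reading of the Bonferroni clause is that it covers pairwise time or group comparisons within an analysis. Nothing extends it over the number of outcomes.

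The main aim itself spans balance, gait, quality of life, cognitive and mental performance and disease severity. The Discussion expects that the programme "can exceed these values of improvement in both dynamic and static balance in single and dual conditions", and also expects better retention at follow-up. These are the authors' expectations, not decision rules, but they show that conclusions beyond the primary outcome are in view. If the primary result were null, the plan as written would still allow a statistically significant finding on some other variable, and no stated rule would mark it as one of dozens of tests.

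**Working it through.** **The plan's own figure.** The only stated error rate is 0.05. For a single test, 1 − 0.95^1 = 0.05, so it holds for one outcome. The plan gives no error rate for the family of outcomes.

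**Step 1: count the non-primary variables in Table 2.** Paired rows count as two. Sway area and the baseline-only COVID questionnaire are left out.

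- Secondary: 7 static CoP variables other than area, 4 stability-limits, 2 rhythmic-shift, Mini BESTest and Tinetti balance = 15.
- Tertiary: 17 gait biomechanics, 2 quality of life (PDQ-39, ABC), 3 cognitive, 2 mood, 2 severity = 26.
- Tinetti gait and FOG-Q are clinical gait scales that the text does not clearly place in a tier: 2.

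The total is 15 + 26 = 41 without those two scales, or 43 with them. Section 2.2.3 records static balance in eight conditions (four Romberg, four functional). Counting the 7 static variables in each gives 7 × 8 = 56, so 34 + 56 = 90, or 36 + 56 = 92.

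**Step 2: chance of at least one false positive.** Assumptions: no outcome is truly affected (the complete null), one test per outcome, normal test statistics with a common correlation ρ, and c = 1.96. The documents give no correlation, so ρ is taken from 0 to 0.8. For m outcomes:

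- Either direction: 1 − ∫ [Φ((c − √ρ z)/√(1−ρ)) − Φ((−c − √ρ z)/√(1−ρ))]^m φ(z) dz
- Benefit only: 1 − ∫ [Φ((c − √ρ z)/√(1−ρ))]^m φ(z) dz

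At ρ = 0 these reduce to 1 − 0.95^m and 1 − 0.975^m. For m = 41 that is 0.878 and 0.646.

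| Outcomes | Direction | ρ = 0 | ρ = 0.2 | ρ = 0.5 | ρ = 0.8 |
|---|---|---|---|---|---|
| 41 | either | 87.8% | 81.5% | 57.7% | 28.2% |
| 41 | benefit | 64.6% | 47.6% | 29.1% | 14.1% |
| 90 | either | 99.0% | 96.6% | 75.4% | 35.0% |
| 90 | benefit | 89.8% | 65.6% | 38.8% | 17.5% |

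Using 43 and 92 changes little: at ρ = 0.5, 58.8% and 75.9% in either direction, 29.7% and 39.1% for benefit.

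**Step 3: what if the MANOVA were a gate?** Suppose single outcomes were read only after a significant MANOVA, with K independent models each at 0.05. The chance that at least one gate opens by error is 1 − 0.95^K: 22.6% for K = 5 and 48.7% for K = 13. Both values of K are assumptions.

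One model for everything does not fit when conditions are counted separately. 92 variables × 2 time contrasts = 184 responses, against 93 − 3 = 90 error degrees of freedom. With each variable entered once, 43 × 2 = 86 responses would barely fit. Smaller models are feasible: one per static condition needs 8 × 2 = 16 responses. Moreover, a gate protects only under the complete null. One real effect opens it for every other variable in the same model.

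**The case against.** Four objections carry weight.

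- **The outcomes are ranked.** There is one primary outcome, it alone is powered, and the rest are explicitly secondary or tertiary. A reader might infer that the plan has no hierarchy at all, and the documents do not support that. What is missing is any use of the ranking in the testing.
- **The 0.05 clause completes the Bonferroni sentence**, and it follows a MANOVA, so the plan is not without safeguards. That is correct. But the Bonferroni is stated for post-hoc comparisons only, and the MANOVA is not stated to be a gate.
- **The percentages in Step 2 are not a model of the plan.** They assume the complete null and one unadjusted test per outcome. This stands, and it is why Step 3 is shown beside them. No further increase is claimed for the follow-up visit, because time is a factor inside the omnibus test.
- **Multiplicity across lower-tier outcomes is commonly left to an analysis plan or full protocol, neither of which is shown.** Silence alone would not be a finding. Here, however, the article sets one level for all analyses and one rule for declaring differences. An outcome-level strategy would have to qualify that text.

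The protocol also commits to publishing all results, including negative or inconclusive ones. This limits selective reporting but does not say which significant results are confirmatory.

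**Conclusion.** The point holds in limited form. Section 2.4 fixes one 0.05 rule for all recorded outcomes, and about 43 non-primary variables (about 92 by condition) fall under it with no stated adjustment across outcomes. Under the complete null with one test per outcome, the chance of some false positive is 28-88% for 41 outcomes and 35-99% for 90, over assumed correlations from 0.8 to 0. With an unstated MANOVA gate and five to 13 independent models, it is about 23-49%.

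A reader might infer that a false claim of benefit is more likely than not. The figures do not support that as a general statement. Counting only the direction of benefit, the chance is 14-65% for 41 outcomes and 18-90% for 90. At correlation 0.5 it is 29% and 39%. For 41 outcomes it is already below one half at correlation 0.2. Many variables come from the same platform recording or gait trial, so substantial correlation is plausible, though the documents give no value. The benefit-direction figures are still well above the 2.5% that a single two-sided 0.05 test allows in one direction.

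**What to change.** In section 2.4, limit the declaration of significance at p < 0.05 to the primary sway-area contrast. Label the secondary and tertiary outcomes exploratory, reported as estimates with 95% confidence intervals and without claims of statistical significance.

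If the sponsor wants confirmatory claims beyond the primary, it should pre-specify a short ordered list drawn from its own secondary tier, tested in fixed sequence at 0.05 and only if the primary is significant. Which outcomes go on the list is the sponsor's choice. Taking them from the secondary tier keeps the trial's own ranking.

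The change is wording in the analysis section and needs no new data. The cost is that significance claims on outcomes outside the primary and any such list are given up.

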### Monitoring

2.5.

No external professionals will be contact for data monitoring procedures. Rather, internal data monitoring is coordinated by a Data Monitoring Committee. For this purpose, one member of each institution of the study integrates the Committee. The monitoring will be independent of the evaluation appointments of this study and will be carried out by telephone monthly to all participants to record the following: (1) changes on Parkinsonian or other medication, (2) falls/week or other adverse events, (3) changes on other therapies (psychology or speech therapy) and neurology appointments, and (4) changes in physical activity outside the study. The Data Monitoring Committee will decide whether trial participation should be discontinued based on the reports from monitoring. The monitoring data will be anonymized and published once the study is over on the trial registration website (clinicaltrials.gov).

## Discussion

3.

Traditionally, balance rehabilitation in people with PD was based on single-task exercises which poses unrealistic scenarios contrary to the complexity of daily life activities where people control multiple systems at the same time in response to multiple stimuli and demands. For this reason, the aim of this study is to quantify the effects of functional balance home training on the biomechanics of balance, gait, general physical status, cognitive performance, and quality of life. Previous authors have considered that including functional tasks in rehabilitation could be more beneficial for people with PD as it guides them back to their everyday lives. In this line, some authors have studied this issue through training with Wii technology (Yen et al., 2011; Zalecki et al., 2013; Carpinella et al., 2017; Negrini et al., 2017; Feng et al., 2019; Yuan et al., 2020), and others have designed easily reproducible training with daily task. However, of these latter authors, only a few have included biomechanical objective outcomes in the evaluation that allow the effects of interventions to be accurately quantified (Smania et al., 2010; Kara et al., 2012; Santos et al., 2017; Soke et al., 2019). The improvements reported by the authors reach 57% on postural stability (Soke et al., 2019), 12,54% (Kara et al., 2012) and 25% (Soke et al., 2019) on LoS exploration, 36,42% (Santos et al., 2017) and 42% (Smania et al., 2010) on CoP sway area, and 40,48% on CoP sway velocity during the Romberg test (Kara et al., 2012). Although the balance changes reported by the studies are significant, the samples of these trials are small and do not include the effectiveness results of patients with cognitive impairment. This aspect is considered in this protocol since epidemiologic studies indicate that the cumulative prevalence of Parkinson’s disease dementia in 8 years is as high as 78.2% and approximately 40% of PD subjects at an earlier stage have a co-existing mild cognitive impairment, boosting the risk of converting to PDD (Fang et al., 2020). This is relevant since the improvement capacity of patients with some cognitive deficit with respect to those with normal cognition is not known even though they have already described the relationship between balance disturbances and cognitive impairment (Saricaoglu et al., 2021). In this sense, home rehabilitation offers an easy alternative for people with PD and their families and can provide greater rehabilitation opportunities and independence for people who must remain at home.

Another relevant aspect is that this protocol aims to solve is the inclusion of dual tasks in the evaluation of balance. Biomechanical balance is usually evaluated as single-tasks on the dynamometric platform (Smania et al., 2010; Kara et al., 2012; Santos et al., 2017; Soke et al., 2019). Complementing the static balance test with dual tasks would provide results of balance performance in real-world situations. Previously, the impact of dual tasks on the gait of trained and untrained people with PD has been determined, finding that verbal secondary tasks have a greater impact on motor performance than visual or motor secondary tasks with the arms (San Martín Valenzuela et al., 2020a,b). In this way, the balanceHOME protocol pretends to resolve methodological issues and research questions relevant to the advancement of physical rehabilitation of balance in the population with Parkinson’s disease.

This protocol will make it possible to facilitate highly challenging functional balance exercises for people with PD at their homes, using common materials of daily use. Similarly, the objective assessment methodology and the balanceHOME protocol will allow us to identify small changes in the balance performance of people with different stages of disease severity and to determine the effectiveness of the home program in people without and with cognitive impairment, which has not been done until now as we will be able to establish the scope that physiotherapy has when it is applied in patients with motor and cognitive failures. Unlike the authors who report improvements below 50% in objective parameters, we think that the structured and progressive dynamics of balanceHOME program can exceed these values of improvement in both dynamic and static balance in single and dual conditions, while performing secondary cognitive and motor tasks of the arms during standing balance maintenance. Furthermore, due to the convenience of home rehabilitation, we think that the effects may achieve better retention during the follow-up period than standard control therapy. This protocol aims to promote change in functional balance physiotherapy both in evaluation and rehabilitation, bringing day-to-day conditions closer to clinical practice.

